# Comparative Evaluation of Effectiveness of Oxygen-Releasing Gel With Scaling and Root Planing (SRP) With That of Scaling and Root Planing Alone in the Management of Chronic Periodontitis Patients: Study Protocol for Cross-Sectional Survey

**DOI:** 10.2196/75795

**Published:** 2026-03-02

**Keywords:** chronic periodontitis, oxygen-releasing gel, antimicrobial properties, wound healing, tissue regeneration, blue m gel, scaling and root planing

## Abstract

**Background:**

Gingival recession and periodontal pockets are the results of the gradual deterioration of the alveolar bone and periodontal ligament caused by periodontitis, which is caused by inflammation of the tissues supporting the tooth. The primary goal of periodontal therapy is to eradicate these aberrant traits. Despite being a popular treatment, scaling and root planing (SRP) has limitations, such as difficulty accessing deeper pockets and root concavities.

**Objective:**

The aim of this study is to assess the effectiveness of oxygen-releasing gel as a supplement to nonsurgical treatment for chronic periodontitis.

**Methods:**

Twenty-two systemically healthy people with sites of chronic periodontitis were the participants of a split-mouth randomized controlled experiment. For every patient, two locations were chosen and divided into two groups at random. In total, 44 sites were chosen and divided into two groups: Group I (the test group) consisted of 22 test sites, while Group II (the control group) consisted of 22 control sites. While group II underwent SRP alone, group I underwent SRP followed by the use of BlueM oral gel. Plaque index, full mouth bleeding score, clinical attachment level, and probing pocket depth were measured at baseline, one month, and three months, and were compared appropriately.

**Results:**

All the clinical measurements will be recorded. It can be anticipated that SRP followed by the use of BlueM oral gel will provide additional benefits in the management of chronic periodontitis by promoting better healing and clinical outcomes.

**Conclusions:**

Within the constraints of this study, it can be anticipated that by encouraging improved healing and clinical results in chronic periodontitis, oxygen-releasing gel is more advantageous when used in conjunction with SRP than when SRP is done alone.

## Introduction

### Background

The hallmark of Stage II Grade A periodontitis, by Panos N. Papapanou et al, a chronic multifactorial inflammatory disease associated with dysbiotic plaque biofilms, is the progressive deterioration of the tooth-supporting framework. Its primary features include gingival bleeding, periodontal pocketing, loss of alveolar bone as seen on radiography, and the loss of periodontal tissue support, as seen by clinical attachment level (CAL) [1]. Removing bacteria and halting the disease’s progression are two primary goals of periodontal therapy. Scaling and root planing (SRP) and other conventional nonsurgical procedures aim to permanently disrupt the biofilm and its maintenance [2]. As it is difficult to lower the bacterial burden because of the complex structure of the root and the location of the deposits, locally injected antimicrobial medications are used either alone or in conjunction with conventional therapy to target the areas of localized periodontal degeneration [3]. It has been recognized as a means of reducing the emergence of resistance, allergic responses, and systemic issues in contrast to systemic antibiotics [4]. At least 700 bacterial species have been found in the oral cavity, making it one of the most complex and varied human microbiomes. A number of these microorganisms are crucial for preserving the health and regular operation of the mouth. Oral conditions like caries, gingivitis, and periodontal disease can result from changes in the ecology of the oral microbiota [5]. Pathogenic bacteria like Capnocytophaga, Leptotrichia, and Fusobacterium can flourish in the anoxic conditions at the biofilm center, whereas oxidative species like Haemophilus, Aggregatibacter, and Neisseriaceae inhabit the oxygen-rich periphery [6]. Gram-negative bacteria, including *Porphyromonas gingivalis*, *Tannerella forsythia*, and *Treponema denticola*, can control the subgingival biofilm in anoxic periodontal pockets due to interactions between proteins and lectins and carbohydrates. Bacterial cells must communicate and signal one another to form biofilms [6]. The immune system and periodontal pathogens interact intricately to define the activity of periodontal disease. The onset and progression of periodontitis have long been linked to changes in the subgingival microbiome. Changes in the polymicrobial population cause disruptions in host homeostasis in vulnerable individuals, and a number of bacteria are commonly linked to periodontal diseases [7]. In the subgingival region, gram-negative anaerobic bacteria interact with the host’s inflammatory responses to create a hypoxic or reduced oxygen environment. Therefore, oxygen is a necessary molecule for life. A variety of physiological or pathological conditions are linked to variations in tissue oxygen requirements [8]. Hypoxia triggers a local defense or protective cellular responses in a chronic inflammatory illness. Such hypoxic reactions could be the pathophysiology of inflammation, which contributes to the pathogenesis and progression of the disease, if the cause of inflammation cannot be eliminated [9]. In the Netherlands, a group of dental surgeons under the direction of [name] created a product that relied on the production of active oxygen [10]. By increasing the oxygen content at the wound site, this oxygen-releasing gel helps to speed up the healing process. Additionally, this high concentration of active oxygen aids in wound healing, bleeding gums, and pocket depth reduction. Using this special mixture lowers the risk of irritation and infections while also improving a person’s dental hygiene. Oxygen is essential for many wound healing processes, including collagen synthesis, bacterial oxidative death, re-epithelialization, and angiogenesis [11]. In order to encourage wound healing, topical and hyperbaric oxygen have both been studied as therapeutic approaches. Therefore, the primary goals of topical oxygen therapy using active oxygen-releasing gel are to promote wound healing and avoid dysbiosis [12]. The purpose of this study is to evaluate how well oxygen-releasing gel works as a local medication to treat chronic periodontitis [13].

### Objectives

To compare the reduction in probing depth following scaling and root planing (SRP) with and without the application of oxygen-releasing gel in the treatment of chronic periodontitisTo evaluate the gain in clinical attachment level after SRP with and without the adjunctive use of oxygen-releasing gelTo assess the reduction in Full Mouth Bleeding Score (FMBS) as an indicator of improved periodontal health following SRP with and without the oxygen-releasing gel

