### Evaluation Outcomes

The primary outcome of this study is to measure probing pocket depth, and secondary outcomes will be PI, FMBS, and CAL.

Secondary outcomes would complement the primary clinical measurements, providing a more comprehensive understanding of how the oxygen-releasing gel contributes to the overall treatment of chronic periodontitis when added to SRP.

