### Strengths of This Study

A randomized controlled trial design, which is regarded as the gold standard for clinical research, is used in this investigation. Dividing individuals into the experimental and control groups at random lowers biases and improves the reproducibility of the findings. Each participant can function as their control thanks to the split-mouth design. As each patient receives both the normal treatment (SRP) and the experimental treatment (oxygen-releasing gel) on separate sides of their mouth, this reduces interpatient variability. Measurable clinical outcomes that are objective indicators of periodontal health and treatment efficacy, like the PI, FMBS, PPD, and CAL, are probably used in this study. This makes it possible to evaluate the oxygen-releasing gel’s effectiveness with clarity.

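### If the trial is split-mouth, as the article says, a full-mouth bleeding score cannot differ between test and control, so objective 3 cannot be answered as written

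*Protocol article*

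**What the plan says.** **Design.** The abstract's Methods paragraph states: "Twenty-two systemically healthy people with sites of chronic periodontitis were the participants of a split-mouth randomized controlled experiment". It continues: "For every patient, two locations were chosen and divided into two groups at random". Strengths of This Study adds that "each patient receives both the normal treatment (SRP) and the experimental treatment (oxygen-releasing gel) on separate sides of their mouth", and Limitations again calls the design split-mouth.

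**Outcome.** The third item under Objectives is to "assess the reduction in Full Mouth Bleeding Score (FMBS) as an indicator of improved periodontal health following SRP with and without the oxygen-releasing gel". Evaluation Outcomes makes probing pocket depth primary and says that "secondary outcomes will be PI, FMBS, and CAL". The abstract reports that "Plaque index, full mouth bleeding score, clinical attachment level, and probing pocket depth were measured at baseline, one month, and three months" and that these measures are compared. Procedure lists FMBS among the clinical characteristics of the participant. No section defines bleeding by site, side or quadrant.

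**Text that points the other way.** Sample size estimations uses the formula for two independent means and arrives at 22 participants per group. Randomization counts 44 participants and uses a coin flip to place people, not sites, into the two groups. Procedure speaks of the patients of Group I and the patients of Group II.

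**The concern.** A between-treatment comparison needs an outcome that can take a different value under each treatment. In a split-mouth trial the unit that receives a treatment is a site or a side, but a whole-mouth score belongs to the patient. It pools the test site, the control site and every other charted point.

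At stake is one of three stated objectives. Followed literally, the plan yields one of two things for bleeding: a null result produced by the arithmetic, or a before-after change with no control. The first could be misread as evidence that the gel does nothing for bleeding, and the second as evidence that it works.

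**Working it through.** **The plan's own figure.** The article gives no figure for FMBS. Its one calculation is the sample size, from Gingival Index means 0.52 and 0.88 and SDs 0.51 and 0.33:

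n per group = (0.51² + 0.33²) × (1.96 + 0.84)² / 0.36² = (0.2601 + 0.1089) × 7.84 / 0.1296 = 22.32

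This agrees with the stated 22, apart from rounding down. It matters here only because the formula treats the groups as independent, which is one of the signs of parallel-group wording. The FMBS point does not depend on it.

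**Between-treatment contrast under split-mouth.** Inputs: 22 patients, each with one test and one control site (abstract), and one FMBS per patient per visit (inferred from the name).

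1. Let F(i,t) be the FMBS of patient i at visit t. The test record and the control record of that patient both hold F(i,t).
2. The reduction from baseline is F(i,0) − F(i,t) in both records.
3. Test minus control is [F(i,0) − F(i,t)] − [F(i,0) − F(i,t)] = 0 for every patient, at one month and at three months.
4. The mean difference is 0 and its SD is 0. The paired t statistic is 0 / (0/√22), which is undefined.
5. The unpaired t test compares two identical copies of 22 values. The difference in means is 0, so t = 0 and P = 1.

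Statistical Analysis lists both t tests. Neither can respond to any gel effect, however large.

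**Change over time under split-mouth.** Let s be the average fall in bleeding from everything except the gel, g the additional fall at gel-treated points (assuming that the gel acts only where it is placed), and w the share of charted points that receive gel. Then:

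expected fall in FMBS = s + w × g

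The trial observes only the sum. Procedure gives every patient brushing instruction, full-mouth supragingival scaling and subgingival treatment, so s is expected to be above zero without any gel. Nothing in a single series of whole-mouth scores separates s from w × g.

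**The parallel reading.** If each participant were in one group only, as Randomization and Procedure are worded, a patient's FMBS would reflect one treatment. The difference in mean reduction between the groups could then be estimated, and objective 3 could be answered. Enrolment does not decide between the readings. The Results section reports 22 participants as of January 2026, which equals the split-mouth total, but recruitment was still open.

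**The case against.** The strongest reply is that the operative sections of the Methods describe a parallel-group trial, in which FMBS is a legitimate patient-level outcome. That part stands, and it makes the point conditional. It does not remove it, because the split-mouth statements are explicit, appear in three places, and are presented as a strength of the trial. The article cannot keep both the split-mouth design and objective 3 as worded.

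A second reply is that the article never defines FMBS, so the one-value reading rests on its name. That is true, but the name says full mouth, Procedure treats it as a participant characteristic, and nothing suggests otherwise.

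A third is that objective 3 says assess where objective 1 says compare, and that Results uses these measures to describe the patient's hygiene state, so a descriptive role may be meant. This has some force, but the with-and-without wording of the objective and the comparison announced in the abstract both imply a contrast.

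Three stronger readings are tempting, and the documents support none of them:

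- **That the authors will enter one score in both groups, or credit its fall to the gel.** No section says so. These are the only results the plan as worded allows, not announced intentions.
- **That the gel's share of FMBS can be sized.** The abstract has one test site per patient, while Procedure applies gel at every site of 4 mm or deeper. The share w is therefore not fixed by the text.
- **That plaque index has the same fault.** The article does not call it a full-mouth score or say how it is aggregated.

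**Conclusion.** The point holds conditionally. Under the split-mouth design, the FMBS contrast between treatments is exactly zero by construction, with zero variance, in all 22 patients and at both follow-up visits. Objective 3 then has no valid between-treatment comparison, and no choice of test repairs that. This is more than detail left to a fuller document, because the stated outcome cannot answer the stated objective under the stated design.

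Two assumptions carry the conclusion: that the trial is split-mouth, and that FMBS is a single whole-mouth value. If the parallel-group wording is the true design, the objective can stand.

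The severity is should-fix. A reader might infer that the trial's main result is compromised, but the documents do not support that. FMBS is secondary, and the primary outcome, probing pocket depth, can be read at the allocated sites, as can attachment level.

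**What to change.** 1. Reconcile the design text first. The abstract, Strengths and Limitations must agree with Sample size estimations, Randomization and Procedure on whether sites or participants are allocated.
2. If the trial is split-mouth, restate objective 3 and the matching secondary outcome as bleeding on probing at the allocated sites, or as percent bleeding on the allocated side if several sites per side are treated.
3. Compare within patient: McNemar or conditional logistic regression for a single site per treatment, and a paired difference for percentages.
4. Keep FMBS as a patient-level description, and state that it carries no between-treatment comparison.

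**Cost.** The wording changes, and readings already taken are re-tabulated. This assumes that the site-level chart behind FMBS is kept, which the article does not say. Data collection was still under way at publication, so the change can be made before analysis.

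**Downside.** A single-site yes/no outcome has limited power. With 22 pairs, only pairs in which one site bleeds and the other does not are informative. Even if all of these favour the gel, exact McNemar gives two-sided P = 2 × 0.5⁵ = 0.0625 with five and 2 × 0.5⁶ = 0.031 with six, so fewer than six cannot reach the 0.05 threshold. Side-level percentages would ease this if several sites per side are treated.

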## Methods

### Overview

This study aims to compare the clinical and microbiological outcomes of SRP with and without the adjunctive use of an oxygen-releasing gel in the treatment of chronic periodontitis.

### Recruitment

Participants in this clinical trial will be those receiving treatment at the Department of Periodontics and Implantology of Sharad Pawar Dental College, Datta Meghe Institute of Higher Education and Research, or those referred for treatment at this institute, who have periodontal pockets larger than or equal to 4 mm in at least ten permanent teeth. All clinical procedures will be performed here. It is thought that this will enhance trial adherence and recruitment because they will already be receiving treatment.

#### Inclusion Criteria

Participants eligible for the study were motivated to undergo therapy and complete follow-up visits. Individuals who provided written informed consent were included. Participants were required to have a minimum of 15 natural teeth and be in good physical and systemic health. Only patients with clinical attachment loss ≥1 mm and diagnosed with chronic generalized periodontitis, presenting with at least 2–3 sites exhibiting periodontal pocket depths ≥4 mm, were selected for the study.

#### Exclusion Criteria

Patients who had undergone periodontal therapy within the previous 6 months or had received antibiotic therapy during the preceding 3 months were excluded. Individuals who were pregnant or lactating, those with known allergies to the study medications, and regular users of mouthwash were also excluded. Additionally, chronic alcohol users were not included in the study.

### Sample size estimations

The sample size was calculated using the formula for comparison of two independent means:

$$\begin{array}{l} n1=(\sigma 12+\sigma 22/\kappa )(Z1-\alpha /2+Z1-\beta )2\Delta 2n_{1}\\ =\frac{(\sigma_{1}^{2}+\sigma_{2}^{2}/\kappa )(Z_{1-\alpha /2}+Z_{1-\beta }{)}^{2}}{\Delta^{2}}n1\\ =\Delta 2(\sigma 12+\sigma 22/\kappa )(Z1-\alpha /2+Z1-\beta )2 \end{array}$$

where n₁ and n₂ represent the sample sizes of groups 1 and 2, respectively; σ₁ and σ₂ denote the standard deviations of groups 1 and 2; Δ represents the expected difference in group means; κ is the allocation ratio (n₂/n₁); Z₁-α/2 corresponds to the standard normal deviate for a two-sided significance level (1.96 for a 95% confidence interval); and Z₁-β represents the standard normal deviate corresponding to the study power (0.84 for 80% power).

Based on previous findings reported by Anuradha et al [14], the mean Gingival Index was 0.52 in group I and 0.88 in group II, with standard deviations of 0.51 and 0.33, respectively. The expected mean difference (Δ) was therefore calculated as 0.36 (0.88 − 0.52). Assuming an allocation ratio (κ) of 1, a power of 80%, and a significance level of 5% (two-sided), the calculated sample size was 22 participants per group.

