A new oxygen-rich mixture called BlueM gel was developed by a team of dentists in the Netherlands. Its main components, sodium perborate and honey enzymes, have combined to create amazing results. This composition is unique in its ability to provide wounded tissues with therapeutically high oxygen concentrations. Along with its oxygen-releasing properties, BlueM gel contains compounds that have antibacterial properties. Its strong bactericidal and bacteriostatic qualities, along with its well-known gradual release characteristic—that is, substantivity within the oral cavity—are what give it its effectiveness [14]. Han et al claim that this gel promotes neovascularization, speeds up the production of new blood cells, and increases stem cell synthesis to produce new fibroblasts [15]. Aqua, alcohol, glycerine, silica, sodium saccharin, sodium perborate, citric acid, PEG-32, sodium gluconate, lactoferrin, xanthan gum, and cellulose gum are the components of the BlueM oral gel recipe, which was developed under [name]’s direction. Each of these chemicals has a specific purpose. BlueM products use oxygen as an active ingredient. Studies show that toothpaste with lactoferrin and active oxygen has similar antiplaque and antigingivitic properties as toothpaste with triclosan. Furthermore, the application of oxygen is essential for a number of healing processes, such as collagen synthesis, angiogenesis, and re-epithelialization [16-18]. Molecular oxygen, one of the wound’s most vital nutrients, is necessary for the healing process [19]. For collagen to be released from cells during the reparative process, oxygen acts as a substrate for the hydroxylation of proline and lysine during collagen synthesis [20]. Oxygen also affects the rates of epithelialization and angiogenesis. When oxygen is given at 1‐2 atmospheres absolute, the oxygen supply regulates the rate of epithelialization in both ischemic and normal wounds [10]. An oxygen gradient stimulates angiogenesis; high arterial PO2~ drives angiogenesis toward areas with low oxygen levels [21]. Molecular oxygen is necessary for leukocytes’ oxidative bacterial killing processes. Bacterial membranes are destroyed by the production of free radicals originating from oxygen. Local oxygen tension is intimately correlated with the rate at which harmful radicals are produced and the capacity to kill through oxidative processes [22]. Investigating topical oxygen treatment may help to lessen wound inflammation and hasten the healing process. According to research, topically administering oxygen promotes the generation of reactive oxygen species (ROS), which are directly related to oxygen levels. Because it may readily pass through cellular membranes, hydrogen peroxide (H2O2) is one of the most prevalent and stable ROS. In tiny quantities, it acts as an intracellular messenger. This property of H2O2 promotes collagen production, stimulates the expression of growth factors such asVEGF (vascular endothelial growth factor) and EGF (epidermal growth factor), controls TGF-β signaling (transforming growth factor–beta), and facilitates neutrophil movement [23]. This study’s findings were comparable to those of a survey by Anuradha et al [14], which compared the effects of curcumin gel as an adjuvant to SRP (Test group) and SRP (Control group). Additionally, Doungudomdacha et al [24] showed statistically insignificant changes in PI and GI (gingival index) in both groups when they compared patients with periodontitis with those with periodontally healthy locations. On the other hand, Koul et al’s survey [10] had different findings that mean difference in GI was greater in the test group than in the control group, even though there was no statistically significant difference in PI between the control and test groups when compared intergroup.

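### The stated 80% power is for a Gingival Index difference that the trial does not measure, so no power or detectable difference is given for the primary outcome, probing pocket depth

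*Protocol article*

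**What the plan says.** The sample-size section of the protocol article names its method: "The sample size was calculated using the formula for comparison of two independent means". Its planning values are "the mean Gingival Index was 0.52 in group I and 0.88 in group II, with standard deviations of 0.51 and 0.33, respectively", credited to reference 14. From these, "The expected mean difference (Δ) was therefore calculated as 0.36". The error rates follow: "Assuming an allocation ratio (κ) of 1, a power of 80%, and a significance level of 5% (two-sided"). The result is that "the calculated sample size was 22 participants per group".

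The section on evaluation outcomes reads: "The primary outcome of this study is to measure probing pocket depth, and secondary outcomes will be PI, FMBS, and CAL". The Abstract, the Procedure section, the Results section and the section on strengths list the same four measures. Gingival Index is in none of these lists. It appears elsewhere only where the Discussion reports other studies.

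The Discussion describes the study with reference number 14 as one "which compared the effects of curcumin gel as an adjuvant to SRP (Test group) and SRP (Control group").

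On design, the Abstract describes a split-mouth trial in 22 people: "In total, 44 sites were chosen and divided into two groups". The section on strengths says that each participant acts as their own control. The Randomization section instead speaks of 44 participants, and the Procedure section of patients in Group I and patients in Group II.

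**The concern.** A power statement belongs to one outcome, one effect size and one analysis. Here the outcome is an inflammation score, while the trial's primary outcome is a depth in millimetres. A difference of 0.36 index units does not convert into a probing-depth difference, and the article gives no probing-depth effect or SD. A reader who sees 80% power next to a probing-depth result would credit the trial with a sensitivity that nobody has calculated.

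Two further features weaken the link between the calculation and the trial. The effect comes from a study described as testing a different adjunct. The formula treats the two arms as independent, so it contains neither a within-patient correlation nor an SD of paired differences, although the Abstract and the section on strengths describe paired sites.

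**Working it through.** **Inputs from the sample-size section.** Means 0.52 and 0.88, SDs 0.51 and 0.33, difference 0.36, allocation ratio 1, z-values 1.96 and 0.84.

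**1. The plan's own figure.**
- Formula: n per group = (SD₁² + SD₂²)(1.96 + 0.84)² / difference².
- Sum of variances: 0.51² + 0.33² = 0.2601 + 0.1089 = 0.3690.
- n = 0.3690 × 7.84 / 0.1296 = 22.32, or 22.35 with exact quantiles.
- Rounded up this is 23; the plan states 22. The figure is reproduced to within one participant per group.
- Power at 22 per group: 0.36 / √(0.3690/22) = 2.78, and Φ(2.78 − 1.96) = 79.4%. A two-sample t test gives 77.5%.

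**2. Outcome used against outcomes planned.**
- Used for sizing: Gingival Index.
- Planned: probing pocket depth (primary); plaque index, full mouth bleeding score and clinical attachment level (secondary).
- The two lists share nothing, so the 80% attaches to no listed outcome.

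**3. Effect of the independent-groups formula if the design is split-mouth.** Keep the Gingival Index inputs and treat the 22 patients as pairs. With within-patient correlation ρ, the variance of a difference is 0.3690 − 2ρ(0.51)(0.33) = 0.3690 − 0.3366ρ. The document gives no ρ, so the values below are assumed. Test: two-sided 5% paired t test, 21 degrees of freedom.

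| ρ (assumed) | SD of differences | Power, 22 pairs |
|---|---|---|
| 0 | 0.607 | 75.5% |
| 0.3 | 0.518 | 87.5% |
| 0.5 | 0.448 | 94.9% |
| 0.7 | 0.365 | 99.3% |

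Power reaches 80% at ρ of about 0.12. Above that, the independent-groups formula asks for more patients than a paired one would.

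**4. What can be said for probing depth.** The article gives no SD, so only a standardised figure follows.
- Split-mouth, 22 pairs: 80% power (two-sided 5% paired t test, noncentral t) needs a mean difference of 0.626 SD of the within-patient differences. For assumed SDs of 0.8, 1.0, 1.2 and 1.5 mm this is 0.50, 0.63, 0.75 and 0.94 mm.
- The other way round, for an assumed true difference of 0.5 mm, power with 22 pairs is 99%, 80%, 61% or 32% if that SD is 0.5, 0.8, 1.0 or 1.5 mm.
- Parallel, 22 per group: 80% power (two-sample t test) needs about 0.86 SD of the outcome. This is the SD between patients, not the SD of paired differences, so the two multiples cannot be compared directly.

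**The case against.** Most of the surrounding criticism can be answered.

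- **Rounding.** The step from 22.32 to 22 costs 0.6 percentage points of power on the normal approximation. The formula was applied correctly, and this would not be a finding alone. That stands.
- **Independent-groups formula.** A reader might infer that it leaves the trial too small. The documents do not support this. On the plan's own inputs, 22 pairs fall short only if the correlation is near zero or negative. If the parallel wording in the Randomization and Procedure sections is the true design, the formula fits it.
- **Curcumin source.** Borrowing an effect from another local adjunct to scaling and root planing is a planning judgement. The Discussion also cites reference 14 for the study gel's own effectiveness, and the source is not at hand. The point adds little beyond showing how remote the effect is from this trial.
- **Reading a null result.** A reader might infer that a null probing-depth result could not be interpreted. It could: the confidence interval for the difference shows which effects are excluded, whatever power was planned.

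None of this touches the main point. The article prints a complete calculation with formula, inputs, source and result, so the fault lies in what it states and not in detail left to a fuller document.

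**Conclusion.** The point holds. The stated 80% power is for a 0.36 difference in an outcome that appears in no list of trial measurements, so it does not apply to probing pocket depth, and neither a power nor a detectable difference is given for that outcome.

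It is tempting to conclude that the trial is underpowered. The documents do not show this: with no probing-depth effect or SD stated, power could be high or low. The millimetre figures above depend wholly on assumed SDs and illustrate the range only.

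The mismatch between an independent-groups formula and a split-mouth design is real if that design is confirmed, but it is conservative on the plan's inputs once within-patient correlation exceeds about 0.12. The shortfall from 80% to 79.4% (77.5% by t test) is minor.

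**What to change.** 1. Reconcile the design first. The Abstract and the section on strengths describe 22 patients, 44 sites and a split mouth. The sample-size, Randomization and Procedure sections read as 22 participants per group, 44 participants, and patients belonging to one group or the other. The power statement cannot be rewritten until one of these is confirmed.
2. Withdraw the 80% claim based on Gingival Index.
3. Before results are seen, state the detectable difference in probing pocket depth for the confirmed design, with an assumed SD in mm, its basis and a range.
   - If split-mouth with 22 pairs: 80% power, two-sided 5% paired t test, for 0.63 SD of the within-patient differences (0.50, 0.63, 0.75 or 0.94 mm for assumed SDs of 0.8, 1.0, 1.2 or 1.5 mm).
   - If parallel with 22 per group: 80% power for about 0.86 SD, two-sample t test.

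The cost is a change of wording. Restating the power does not itself require extra patients. The restated figure may look less favourable than 80%. It will describe what the confirmed number can detect, and will not show that this number was chosen for probing depth.
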